### **5.3. PRIMARY DATA ANALYSES**

The percentage of 'asthma ever' reported at five years will be presented separately for children in the treatment and non-treatment groups. Comparison between the treatment arms will be estimated using binary regression adjusted for the randomisation stratification factor of birth mode. Results will be presented as adjusted risk difference and its 95% confidence interval (CI). The analysis will be presented as ITT with multiple imputation as described above.

The two other stratification factors used for randomisation (site and plurality) will not be included in adjustments because it is already known from Part 1 that 98.3% of infants were singleton and 95.2% were from the same site .

As a sensitivity analysis, the same binary regression model will be re-run excluding the 7-10 year follow-up questionnaire data.

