## 2.3. STUDY POPULATION

1,272 healthy newborns were randomised, within 10 days of birth, in a 1:1 ratio, to study group 1 (BCG, n=637) or study group 2 (no BCG, n=635). Twin pairs were randomised to the same group but only one twin from each pair was included as a study participant, regardless of birth order. A total of 21 sets of twins were randomised in the trial and 17 sets of twins continued into Part 2.

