#### **Multiple Imputation**

The primary analysis will be an intention-to-treat analysis. It is already known that the proportion of missing data for the primary outcome will be more than 5%, due to loss to follow-up. To adjust for this selection bias (collider stratification bias), multiple imputation models will be conducted for the outcome variables and 50 completed data sets will be imputed by chained equations including all the children initially randomised. The primary outcome, strata variable (mode of birth: vaginal/caesarean), and the variables associated with either remaining in the study or asthma listed below will be included in the imputation model. Although there are two other randomisation strata (study site and singleton/twin), the number of participants recruited at study sites other than the Mercy, and the number of twins, is so small that it is not possible to multiply impute separately for these strata.

The directed acyclic graph (DAG) below summarizes the expected associations between variables, including the open front door path created by restriction on the collider 'remain in the study' caused by loss to follow-up and incomplete data. The multiple imputation aims to impute the missing data for those who did not remain in the study. By including variables that are expected to be associated with both remaining in the study and the outcome, the restriction on 'remain in the study' is removed and this open path is closed.

[figure not shown]

Informed by the DAG, and in order of priority, the variables listed below may be included in the multiple imputation. If necessary, the number of categories included in categorical variables will be reduced to allow the multiple imputation to run.

| Variable                        |                        | Definition                                                                                                                                                                                    |
|---------------------------------|------------------------|-----------------------------------------------------------------------------------------------------------------------------------------------------------------------------------------------|
| Maternal education              | Generated, categorical | Three categories – below year 10, year 12/trade certificate or university educated.                                                                                                           |

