#### 5.2.4. SUBGROUP ANALYSIS

Additional adjusted models will be estimated to explore the potential heterogeneity of the effect of the intervention. Each model will include as covariates the mode of birth stratification factor, and an interaction term estimating the interaction between the intervention and the sub-group variable (listed below). Where the models provide evidence that the intervention varies between sub-groups, the intervention effect in each sub-group and their 95% confidence intervals will be

presented, together with the p-value for the intervention-by-subgroup interaction, as a guide to the strength of the evidence for an interaction. All sub-group analysis will be conducted on the imputed data.

Sub-groups are variables that are known or suspected risk factors for asthma in childhood that are also known or suspected to influence the immune response to BCG vaccination. Sub-group analysis will include:

1. Either parent has a history of asthma
2. Sex
3. Maternal history of BCG vaccination

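### The outcome models adjust for birth mode only and forgo a small, inexpensive gain in precision from sex and parental asthma

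*SAP*

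**What the plan says.** Section 5.3 fixes the primary model: "Comparison between the treatment arms will be estimated using binary regression adjusted for the randomisation stratification factor of birth mode". The result is an adjusted risk difference with a 95% confidence interval, after multiple imputation. Section 5.4 repeats this model for every secondary outcome. The only sensitivity analysis in 5.3 drops the 7–10 year questionnaire; none adds covariates.

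On the remaining strata, 5.3 says "The two other stratification factors used for randomisation (site and plurality) will not be included in adjustments" and gives the reason: "it is already known from Part 1 that 98.3% of infants were singleton and 95.2% were from the same site". The Multiple Imputation part of 5.2.3 gives a similar reason, that the number in these strata "is so small that it is not possible to multiply impute separately for these strata".

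Section 5.2.4 says: "Sub-groups are variables that are known or suspected risk factors for asthma in childhood". The list that follows includes sex and a history of asthma in either parent. The variable table in 5.2.3 also lists sex and family history of asthma, the latter counting mother, father or sibling. The listed variables are candidates, in order of priority, that may enter the imputation. The SAP does not say why sex and parental asthma stay out of the outcome models.

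**The concern.** A covariate that predicts the outcome explains part of its variance, and adjusting for it tightens the estimated treatment effect at no recruitment cost. The SAP treats sex and parental asthma as prognostic and has both in hand, yet uses them only for subgroups and possibly for imputation.

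Precision matters in this trial. Section 2.4 counted on 1,294 children at five years, but section 2.1 reports 1,272 randomised and 1,027 consenting to Part 2. Recruitment cannot be reopened, so the analysis is one of the few places where information can still be gained. At stake is the width of the interval, not the validity of the comparison.

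**Working it through.** **Inputs from the SAP.** Planned 1,438 with 90% retained; asthma ever 22% against 16% (2.4). Randomised 637 and 635 (2.3). Consenting to Part 2: 1,027 (2.1). Singletons 98.3% and main site 95.2% (5.3). "A total of 21 sets of twins were randomised in the trial and 17 sets of twins continued into Part 2" (2.3).

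**Assumptions, not in the SAP.** Two-sided 5% test (2.4 gives neither power nor alpha for asthma); equal arms; overall risk 19%, the mid-point of 22% and 16%; family history in 40% of children; half of them male; odds ratios 1.5 to 3 for family history and 1.3 to 1.6 for sex. Family history stands in for parental history.

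**1. The plan's own figure.** 1,438 × 0.9 = 1,294.2, or 647 per arm. Power = Φ[(d − 1.96·SE0)/SE1], where
- SE0 = √(2 × 0.19 × 0.81/647) = 0.0218
- SE1 = √[(0.22 × 0.78 + 0.16 × 0.84)/647] = 0.0217
- d = 0.06

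This gives 78.6%, so the stated 6-point difference fits a conventional 80% target approximately. The same formula gives 77.9% at 1,272 and 68.9% at 1,027.

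**2. Variance explained by the two covariates.** R² is the variance of the risk across the four sex-by-history cells, divided by 0.19 × 0.81 = 0.1539. Cell weights are 0.3, 0.3, 0.2, 0.2 (no history female, no history male, history female, history male; male taken as the higher-risk sex).
- Weak case (odds ratios 1.5 and 1.3): risks 14.7%, 18.3%, 20.5%, 25.1%; variance 0.00137; R² = 0.0089.
- Strong case (3 and 1.6): risks 9.7%, 14.7%, 24.4%, 34.0%; variance 0.00825; R² = 0.0536.

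**3. Effect on precision.** The standard error is multiplied by √(1 − R²), which is equivalent to dividing n by (1 − R²).

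| | Weak | Strong |
|---|---|---|
| Standard error smaller by | 0.4% | 2.7% |
| Power at 1,027 (68.9% unadjusted) | 69.3% (+0.4) | 71.3% (+2.4) |
| Power at 1,272 (77.9% unadjusted) | 78.3% (+0.4) | 80.1% (+2.2) |
| 95% half-width at 1,272 (4.30 points unadjusted) | 4.28 | 4.18 |

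**4. Cross-check by simulation.** 2,000 trials per scenario were run with n = 1,272, complete outcomes and a linear risk-difference model with robust standard errors. With risk ratios of 1.5 for sex and 2 for family history (prevalence 35%), the mean standard error fell from 0.0219 to 0.0215 and power rose from 78.6% to 79.6%. The most favourable scenario (risk ratio 3 for family history) gave 0.0220 to 0.0210, about 4%, and 77.8% to 81.4%. The mean risk difference stayed at about −0.060 with and without the covariates, so the omission causes no bias.

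**5. Site and plurality.** 1 − 21/1,272 = 98.3%, which reproduces the singleton share. For a binary factor with prevalence q and risks r1 and r0, R² = q(1 − q)(r1 − r0)²/[p(1 − p)]. With an assumed risk ratio of 1.5 to 2 and p = 0.19 to 0.22, the interval narrows by 0.05% to 0.2% for plurality (q = 0.017) and by 0.1% to 0.6% for site (q = 0.048).

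**The case against.** The strongest objection is that nothing here is wrong. The model is clear and prespecified, and leaving prognostic covariates out of a randomised comparison does not bias the risk difference. The gain is small beside the 9.7 points of power separating 1,294 children from 1,027 (78.6% − 68.9%), and it rests on odds ratios the SAP does not supply. All of that stands, and it makes this an optional improvement.

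Multiple imputation adds uncertainty. The analysis imputes all 1,272 children, while 1,027 is the number consenting to Part 2, not the number with an observed outcome. The net gain after imputation was not simulated. Sex and family history may already inform the imputed values, but the SAP only says they may be included, so a reader should not take their use as settled.

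A reader might also infer that site and plurality should be restored because randomisation was stratified on them. It is true that "it is not possible to multiply impute separately for these strata" rules out separate imputation and not a simple covariate. But 5.3 gives an explicit reason for leaving them out, and the gain is well under 1%. A twin term also carries a risk: 17 twin sets, one participant each, give about 17 × 0.19 = 3.2 events for the primary outcome. For a severe-asthma outcome at an assumed 5% to 10%, the chance of no twin event is 0.95^17 = 42% to 0.90^17 = 17%. The twin coefficient could then not be estimated, and standardisation does not cure that.

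Finally, 5.1 says the trial statisticians already know the allocation, so late covariate choices carry some credibility cost. It is limited here because the SAP already names both variables, on subject-matter grounds.

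**Conclusion.** The point holds as a minor efficiency improvement. The models in 5.3 and 5.4 are valid and unbiased, but they leave out two predictors that the SAP itself regards as prognostic. The cost is about 0.4% to 2.7% of the standard error, or roughly 0.4 to 2.4 points of power, under the stated odds ratios and before allowing for imputation. The most favourable simulated scenario reaches about 4% and 3.5 points.

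The documents do not support reading this as an error, a source of bias or a contradiction, nor as a case for adding site and plurality.

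**What to change.** Before the Part 2 data are unblinded:

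- In 5.3 and 5.4, state that the risk difference is obtained by standardising, over the sample, a logistic model with treatment, birth mode, sex and parental history of asthma as recorded at baseline. This keeps the risk-difference measure and avoids the fitting difficulties that an identity-link model can meet with more covariates.
- Fix one definition of family history and its time point. The table in 5.2.3 counts siblings and gives no time point; 5.2.4 counts parents only.
- Make these covariates definite members of the imputation model, and pool the standardised estimates by Rubin's rules.
- Keep the birth-mode-only model as a supporting analysis. If the sponsor prefers not to change the primary model, the adjusted version can be prespecified as the supporting analysis instead.
- Leave site and plurality out, as 5.3 already does.

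The cost is a few sentences in the SAP, slightly more code and a departure from the simpler model.

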### **5.4. SECONDARY DATA ANALYSES**

For each secondary outcome, the percentage of study participants with the outcome will be presented separately for children in the treatment and non-treatment groups. Comparison between the treatment arms will be estimated using binary regression adjusted for the randomisation stratification factor of birth mode. Results will be presented as adjusted risk difference and its 95% confidence interval (CI).

Intention to treat analysis with multiple imputation will be used for all the secondary outcomes.

### **5.5. ANALYSIS OF OTHER OUTCOMES**

For other outcome variables, the percentage of study participants with the outcome will be presented separately for children in the treatment and non-treatment groups. No formal statistical comparisons will be made.

